### Sample size and statistical analyses

Based on previous estimations, we expect the risk of renewed self-harming acts within their first year to be 50 percent in the CAMS treatment group
[6]. We expect the DBT to be able to reduce this risk to 25 percent, a relative risk reduction of 50%. With a power of 90% and a type one error probability associated with this test of 0.05, we plan to randomize 154 patients, with about 77 patients in each intervention group. We will handle missing data using logistic regression with multiple imputations as described below.

The two group baseline characteristics will be compared using Student’s *t*-test for independent samples or a chi-square test for binary variables.

The primary analysis will be based on the intention-to-treat principle; that is, data from all patients will be included in the treatment group to which they were allocated regardless of degree of compliance.

Binary outcomes will be analyzed using logistic regression and continuous outcomes will be analyzed using linear regression with baseline variables as sex and previous deliberate self-harm as a covariates.

If more than 5% of the primary outcome is missing at follow-up, we will use multiple imputations (SPSS version 19.0). If this is the case, the multiple imputations will be considered the primary result. For multiple imputations, we will use a linear regression model with 100 imputations and 20 iterations. The pooled estimates from the imputations will subsequently be used for our analysis.

We will use two-tailed tests for statistical significance with alpha set at *P* <0.05.

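### The only imputation model named for the binary primary outcome is a linear regression, which cannot produce yes/no values for the planned logistic analysis

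*Protocol article*

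**What the plan says.** All the imputation rules stand in the protocol article under Sample size and statistical analyses.

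- **Opening statement:** "We will handle missing data using logistic regression with multiple imputations as described below".
- **Analysis model:** "Binary outcomes will be analyzed using logistic regression", with sex and previous self-harm as covariates. Continuous outcomes get linear regression.
- **Trigger and status:** if more than 5% of the primary outcome is missing, multiple imputation is used and its result is the primary one.
- **Imputation model:** "For multiple imputations, we will use a linear regression model with 100 imputations and 20 iterations".
- **Pooling:** "The pooled estimates from the imputations will subsequently be used for our analysis".

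The opening of Methods/Design defines the primary outcome as the share of participants with an attempt or a self-harm act up to week 28, which is yes or no for each person. The sample size uses the same scale: "we expect the risk of renewed self-harming acts within their first year to be 50 percent in the CAMS treatment group", against 25% with DBT. The abstract (a ratio of acts) and the Primary outcome section (a before/after ratio) word the outcome differently.

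**The concern.** The trigger concerns missing primary outcome data, so the linear model applies to that variable and cannot be read as covering only the symptom scales. For a yes/no outcome, such a model draws from a normal distribution around a fitted mean. The draws are continuous and many are negative or above 1. They cannot enter an ordinary binary logistic regression until someone decides how to turn them into events and non-events, and the article gives no rule.

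This would not be a side analysis. Above a low threshold it supplies the trial's primary result, and the Discussion relies on multiple imputation to limit bias from missing data. The conversion rule would then be chosen after the data are in.

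The pooling sentence adds a smaller problem. It places pooling before analysis, whereas in multiple imputation each completed data set is analysed first and the estimates are combined afterwards.

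**Working it through.** **Inputs from the article.** Risks 0.50 (CAMS) and 0.25 (DBT); 90% power; two-sided alpha 0.05; 154 patients, 77 per arm; logistic analysis adjusted for sex and previous self-harm. The stated risks are for the first year, while the primary time point is week 28; they are used here as stated.

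**1. The plan's own figure.** Two proportions, pooled variance, no continuity correction:

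n = [1.96·√(2·0.375·0.625) + 1.2816·√(0.50·0.50 + 0.25·0.75)]² / 0.25² = (1.3419 + 0.8477)² / 0.0625 = 76.7, so 77 per arm and 154 in total.

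This matches the article. The sample size therefore rests on a binary outcome.

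**2. When the rule applies.** 7/154 = 4.5% and 8/154 = 5.2%, so 8 missing outcomes are enough. (With the 160 given in the abstract it takes 9: 9/160 = 5.6%.)

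**3. What a linear model draws.** Take Normal(p, √(p(1−p))).

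- p = 0.25, SD 0.433: P(<0) = Φ(−0.577) = 0.282; P(>1) = 1 − Φ(1.732) = 0.042; outside the range 0.323.
- p = 0.50, SD 0.500: 2·Φ(−1) = 0.317 outside the range.

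In the simulation below, where one residual SD is fitted to both arms, 33% to 34% fell outside. The remaining draws are fractions.

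**4. Effect of rounding at 0.5.** At p = 0.25, P(≥0.5) = 1 − Φ(0.577) = 0.282. At p = 0.50 it stays 0.500. A true 25% is thus imputed as 28.2%, but only among the imputed patients. The whole-arm DBT risk becomes 0.9·0.25 + 0.1·0.282 = 25.3% at 10% missing and 0.7·0.25 + 0.3·0.282 = 26.0% at 30% missing.

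**5. Simulation.** 154 patients, 800 replicates per scenario, 30 imputations (not 100, for speed), estimates combined by Rubin's rules. Assumptions that are not in the article: missing completely at random at 10%, 20% or 30%; 25% in one sex stratum; 60% with multiple previous acts; log odds ratio 0.6 for previous acts.

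| Missing | Log OR, complete data | Log OR, linear and rounded | Shrinkage | Power, linear and rounded | Log OR, logistic imputation | Power, logistic imputation |
|---|---|---|---|---|---|---|
| 10% | −1.130 | −1.111 | 0.019/1.130 = 1.7% | 84.9% | −1.139 | 86.3% |
| 20% | −1.145 | −1.102 | 0.043/1.145 = 3.8% | 79.2% | −1.159 | 81.6% |
| 30% | −1.136 | −1.067 | 0.069/1.136 = 6.1% | 70.4% | −1.149 | 75.8% |

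Most of the fall in power comes from the missing data themselves. The part due to the linear model is 1.4, 2.4 and 5.4 percentage points. Both methods were run on the same simulated data sets; the Monte Carlo error of one power figure near 80% is √(0.8·0.2/800) = 1.4 points.

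**6. Standard errors.**

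- *Rubin combination, linear and rounded:* mean SE against empirical SD is 0.381/0.377, 0.404/0.397 and 0.428/0.419. Coverage is 95.0% to 95.8% and type I error 3.6% to 5.0%. Nothing is wrong here.
- *Imputed values averaged first, then one analysis:* SE 0.362, 0.363 and 0.363 against SD 0.386, 0.417 and 0.451. Type I error is 6.2%, 8.9% and 10.5%. As a rough check, with the SE too small by √(1−m), 2·[1 − Φ(1.96·√(1−m))] gives 6.3%, 8.0% and 10.1%. Rounding those averages as well would raise it to 14%, 23% and 30%, but the article describes neither step.

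**The case against.** **The two statements need not conflict.** A reader might infer a flat contradiction between the opening logistic statement and the linear model below it. The text does not force that. The opening can mean a logistic analysis applied to multiply imputed data, which agrees with the rule for binary outcomes. What stands is that it refers the reader to a description that names only a linear model.

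**Standard errors.** A reader might also infer that the planned confidence intervals are too narrow. The article speaks of pooled estimates, not averaged values, and that is the usual term for results combined across imputed data sets. On that reading coverage and type I error are close to nominal, even with linear imputation and rounding. The wording leaves the order open and needs tightening, but it does not establish invalid inference.

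**The outcome is not worded as binary throughout.** Under the abstract or the Primary outcome section, a linear model would not be plainly wrong. This stands as a separate point to align. It does not rescue the rule, because the sample size fits only the per-participant reading.

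**The bias is small and towards no difference.** This also stands. In the simulation, a logistic fit that tolerates fractional outcomes did well too (coverage about 95%), but that is a different analysis from the one the article plans.

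**An analysis plan may settle this.** It would have to override a model that the article names, so this is more than detail left to a later document.

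**Conclusion.** The point holds in a limited form. The article names an unsuitable imputation model for an outcome that it defines per participant, sizes as a risk and would analyse by logistic regression. That model would produce the primary result from 8 missing outcomes onward. No imputed value would be a valid outcome without a conversion rule, and none is given.

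With rounding at 0.5, the cost is about 2%, 4% and 6% of the log odds ratio and 1.4, 2.4 and 5.4 points of power at 10%, 20% and 30% missing. These sizes rest on assumed missing shares, data missing completely at random, the article's first-year risks and the assumed covariate effects. Type I error would rise, to about 6% to 10%, only if imputed values were averaged before a single analysis, which the article does not say. This should be fixed; it does not undermine the design.

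**What to change.** Replace the sentences on the imputation model and on pooling with:

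> Participants with any recorded act up to week 28 are classified as events. A missing binary primary outcome is imputed by logistic regression including arm, sex and previous self-harm; linear regression imputation is used only for continuous scales. The logistic analysis model is fitted in each of the 100 imputed data sets, and the log odds ratios and standard errors are combined by Rubin's rules.

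Self-harm by week 17 should not be added as a predictor in this model. Under the Methods/Design definition such an act already makes the outcome an event, so the predictor would separate the outcome perfectly. Those participants are classified, not imputed.

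The abstract and the Primary outcome section should be brought into line with the per-participant definition at the same time.

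The cost is a few sentences, settled before unblinding. The sample size stays at 154 and no new data are needed. In the simulation, logistic imputation kept the log odds ratio close to its complete-data value, with coverage of 95.2% to 95.5% and type I error of 4.1% to 5.6%.

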### Ethical considerations

The trial protocol is approved by the regional ethics committee in the Capital Region of Denmark under file number H-1-2011-042. The Danish Data Protection Agency has approved the management of data in the trial under the file number 2007-58-0015. Finally, the trial is registered under ClinicalTrial.gov as NCT01512602. In accordance with the CONSORT guidelines
[41], we will publish negative, neutral and positive findings in the trial.

We have decided not to have a control group without any intervention, because of the ethical aspects when treating suicidal and vulnerable patients.

The patients will be informed about the trial with both verbally and with written information before signing the written consent. It will be stressed that participation in the trial is voluntary. Participation and the written consent can be withdrawn at any time in the trial, and this can be done with no consequence for future treatment possibilities.

## Discussion

The DiaS trial is designed as a pragmatic trial, with the intention of intervening in the exiting clinical outpatient setting, so one could argue the patient population is selected beforehand. The Excellence Centre for Suicide Prevention has their exclusion criteria before offering treatment as mentioned before and can exclude patients for whom treatment can appear too demanding. The chosen target group includes patients with emotional dysregulation leading to suicide attempts. This patient group is over-represented in the Centre of Excellence in Suicide Prevention. The chosen experimental DBT treatment is based on a modified DBT manual but where all the skills taught are maintained. The DBT treatment period of 16 weeks is shorter than in the majority of other randomized clinical trials performed
[16]. The considerations of these modulations are the excepted occurrence of the lesser chronicity and severity in BPD symptoms in the target group of patients. The patients only have to fulfill two out of nine BPD criteria according to the DSM-IV. Regarding the CAMS-informed supportive psychotherapy given to the control group, this treatment has been an obvious choice as the majority of therapist in the Excellence Centre for Suicide Prevention use this treatment. This treatment group can be considered as an optimized ‘treatment-as-usual’ control group, where the therapists are trained and supervised, and treatment adherence is rated.

The two different intervention groups will receive different amounts of time of individual psychotherapy, and the CAMS group is not offered skill training in groups. We consider the different amounts of time in the two groups as inevitable because of the different basic construction of the two psychotherapeutic treatments. In the CAMS- intervention group the therapist has to finish the treatment when achieving three consecutive non-suicidal scores on the SSF. A strength of this trial is the centralized randomization
[42], which reduces the risk of selection bias. We will perform blinded outcome assessment to reduce bias
[43]. We will use intention-to-treat analysis and multiple imputations to reduce the bias introduced by missing data in our analysis
[43].

A related post-hoc consideration is the potential ‘cost-effectiveness’ of the respective treatments in relation to frequencies of hospitalizations, emergency department visits, and primary care visits. The cost-effectiveness of clinical care for high-risk patients was previously examined in a retrospective study of CAMS versus treatment-as-usual with suicidal outpatients
[44] and is a topic of increasing importance within contemporary mental health care around the world.

The DiaS trial is a single center trial and can therefore be considered as a pilot trial for multicenter trials in the future. In order to obtain external validity, we need multicenter trials. The DiaS trial has a 52-week follow-up period to investigate deliberate self-harm and suicide attempts after treatment. This knowledge can be useful in the design of trials, in regard to treatment duration or to booster treatment sessions. Moreover we need trials showing comparable effects both during the intervention period and the post-intervention period.

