## Abstract

**Background:**

In Denmark 8,000 to 10,000 people will attempt suicide each year. The Centre of Excellence in Suicide Prevention in the Capital Region of Denmark is treating patients with suicidal behavior, and a recent survey has shown that 30% of the patients are suffering from borderline personality disorder. The majority of patients (70% to 75%) with borderline personality disorder have a history of deliberate self-harm and 10% have a lifetime risk to die by suicide. The DiaS trial is comparing dialectical behavior therapy with collaborative assessment and management of suicidality-informed supportive psychotherapy, for the risk of repetition of deliberate self-harm in patients with a recent suicide attempt and personality traits within the spectrum of borderline personality disorder. Both treatments have previously shown effects in this group of patients on suicide ideation and self-harm compared with treatment as usual.

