### Inclusion and exclusion criteria in the DiaS trial

#### Inclusion criteria

1) 18 to 65 years of age.

2) Recent suicide attempt within one month from the inclusion date.

3) At least two of the following criteria for borderline personality disorder (DSM-IV)^a^:

a) Desperate efforts to avoid being betrayed or abandoned in reality or in imagination.

b) A pattern of unstable and intense interpersonal relationships characterized by a swinging between extremes of idealization and devaluation.

c) Identity disturbance: markedly and persistently unstable self-image or self-feeling.

d) Impulsivity in at least 2 areas that are potentially self-harming (for example, sexual misconduct, abuse, consumption, and overeating).

e) Repeated instances of suicidal behavior, gestures or threats or self-harm.

f) Affective instability.

g) Chronic feelings of emptiness.

h) Inappropriate intense anger or difficulty controlling anger.

i) Transient, stress related paranoid ideation, delusions or severe dissociative symptoms.

4) Informed consent.

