#### Exclusion criteria

– Severe depression.^b^

– Bipolar disorder.^b^

– Psychosis in schizophrenia spectrum.^b^

– Anorexia nervosa.^b^

– Alcohol or drug addiction.^b^

– Mental retardation.

– Dementia.

– Insufficient ability in speaking and understanding Danish

– Lack of informed consent.

^a^Assessed by SCID-II
[26].

^b^Assessed by Mini International Neuropsychiatric Interview (MINI)
[25].

All psychiatric departments in the Capital region of Denmark have been informed of the DiaS trial through meetings and leaflets (see inclusion criteria above). Patients with at least two traits from the BPD diagnosis (DSM-IV)
[3] and a recent suicide attempt are referred through the Centre of Excellence in Suicide Prevention. The suicide attempt has to be within a month from the first contact with the Centre. The date has been selected to ensure the accuracy of reporting the intent and other important circumstances (feelings, thoughts and behavior prior to, at the time of, and after the suicide attempt). The patients must speak and understand Danish sufficiently to participate in the therapy sessions and the assessment of the trial. The diagnostic criteria for exclusion have been chosen to eliminate potential confounders in the trial and ensure a homogenous group of patients.

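### Eligibility runs from two BPD criteria to full BPD, yet the baseline criterion count is not in the primary model and the Discussion describes a milder group

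*Protocol article*

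**What the plan says.** The inclusion criteria require a recent suicide attempt ("Recent suicide attempt within one month from the inclusion date") and at least two of the nine DSM-IV BPD criteria, assessed by SCID-II. No maximum is given, and full BPD is not in the list of exclusions. One of the nine, criterion (e), is "Repeated instances of suicidal behavior, gestures or threats or self-harm".

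The Discussion explains the modified 16-week DBT by an expectation of less chronic and less severe BPD symptoms in the target group, and adds: "The patients only have to fulfill two out of nine BPD criteria according to the DSM-IV". The Abstract reports, for the Centre that supplies the patients, that "30% of the patients are suffering from borderline personality disorder".

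Under Randomization and blinding, the strata are sex and number of previous self-harm acts (single or multiple). Under Sample size and statistical analyses, the regression models are specified "with baseline variables as sex and previous deliberate self-harm as a covariates". The BPD criterion count appears in neither place, although the SCID-II is part of the screening interview described under Recruitment.

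**The concern.** Two things do not fit together. The treatment rationale speaks of a milder group, while the entry rule admits any number of criteria from two to nine. The Discussion cites a minimum as if it described the typical patient, and nothing in the criteria makes the enrolled group milder.

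The variable that would describe this spread is measured before randomization but unused in the stated primary model. BPD severity plausibly predicts the primary outcome, so a chance difference in severity between arms would pass into the treatment estimate uncorrected. A reader of the result could also take it as applying to milder patients only, because that is how the article describes the target group.

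Precision and description are at stake, not the validity of the comparison.

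**Working it through.** **1. The plan's own figure.** Inputs from Sample size and statistical analyses: risk 0.50 with CAMS, 0.25 with DBT, power 90%, two-sided alpha 0.05. With pooled variance and no continuity correction, the mean risk is 0.375 and

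n = [1.96·√(2·0.375·0.625) + 1.2816·√(0.5·0.5 + 0.25·0.75)]² / 0.25² = (1.342 + 0.848)² / 0.0625 ≈ 76.7, so 77 per arm and 154 in total.

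This matches the article, and power at 77 per arm is 0.901. The point concerns no arithmetic error.

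**2. Who can enter.**
- Repeat attempter or self-harmer: in effect meets (e), so needs one further criterion.
- First-time attempter with no other self-harm: needs two criteria other than (e).
- Upper end: all nine criteria.

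A count that leaves out (e) therefore runs from 1 to 8 among eligible patients.

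**3. Chance imbalance in severity.** The article gives no trait distribution for participants, so the share w in a more severe group is assumed. With 77 per arm and no stratification on severity, SE = √(2·w(1−w)/77):

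| Assumed w | SE | 95% range |
|---|---|---|
| 0.30 (the Centre-wide BPD share) | 0.074 | ±14.5 points |
| 0.50 | 0.081 | ±15.8 points |

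**4. What such an imbalance would move.** Assume half the patients are more severe, overall risk is 50%, and the odds ratio between severity and outcome is 2 or 4.
- Odds ratio 2: odds 0.707 and 1.414, risks 0.414 and 0.586, gap 0.172. A 15.8-point imbalance shifts the contrast between arms by 0.158 × 0.172 = 2.7 points.
- Odds ratio 4: odds 0.5 and 2, risks 0.333 and 0.667, gap 0.333. The shift is 0.158 × 0.333 = 5.3 points.

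The planned difference is 25 points. These shifts are at the edge of the 95% range.

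**5. Power and type I error.** Logistic regression was simulated with 154 patients, a 50/50 severity split, overall risks of 50% and 25%, and 2,000 runs per setting:

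| Severity odds ratio | Power without | Power with | Type I error without | Type I error with |
|---|---|---|---|---|
| 1 | 0.902 | 0.895 | 0.042 | 0.046 |
| 2 | 0.897 | 0.898 | 0.053 | 0.057 |
| 4 | 0.901 | 0.927 | 0.045 | 0.047 |

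The Monte Carlo standard error of each power figure is about √(0.9·0.1/2000) = 0.007. The gain is nil at an odds ratio of 2 and about 3 points at 4. The comparison model here contained treatment only. The planned model already has previous self-harm, which probably correlates with the trait count, so the real gain may be smaller.

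**6. Precision of a severity interaction.** With the 154 split evenly by severity, there are 38.5 patients per arm in each half. At risks of 0.50 and 0.25 in both halves, the variance of the log odds ratio in one half is 1/(38.5·0.25) + 1/(38.5·0.1875) = 0.104 + 0.139 = 0.242. The interaction has SE √(2·0.242) = 0.70, so its 95% interval spans a factor of exp(1.96·0.70) ≈ 4 in each direction.

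**The case against.** The best reply is that the article never hides its population. The Abstract and Background describe a borderline spectrum and a minimum of two traits. The Discussion states an expectation about the group as a whole, not an eligibility rule, and the Background gives a separate reason for 16 weeks: most of the gain from DBT comes in the first four months. Criterion (e), the trait tied most closely to the outcome, is already covered by the self-harm stratum and covariate. Leaving out a prognostic covariate is no error in a randomized trial, because chance imbalance is already allowed for in the standard error. Extra covariates could also be set in an analysis plan that is not shown.

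Most of this stands, and it limits the point to an improvement. It does not remove it: the article does name its model covariates, and the trait information beyond (e) is not among them.

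Stronger readings that a reader might infer, and why the documents do not support them:
- *Some participants have almost no BPD traits.* Everyone must meet two criteria.
- *The primary result is unadjusted.* The model includes sex and previous self-harm.
- *The uneven entry threshold for first-time and repeat attempters distorts the comparison.* That difference follows the self-harm stratum, which is balanced by design and adjusted for.
- *The Exclusion criteria section contradicts the entry rule when it says that it will* "ensure a homogenous group of patients". The subject of that sentence is the diagnostic exclusions, such as psychosis and addiction, not BPD severity.
- *A known number of participants has full BPD.* The 30% is a share of the Centre's patients. No distribution is given for those enrolled.
- *The trial is underpowered because milder patients have lower risk.* If CAMS risk were 40% or 30% with the same 50% relative reduction, power would be 0.78 or 0.61. The article gives no risk by severity, and a covariate would not cure this.

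**Conclusion.** The point holds as a modest improvement. Eligibility has a floor and no ceiling, the Discussion's account of a milder group is not enforced by it, and a plausibly prognostic baseline value already collected is absent from both the strata and the named covariates. The randomized comparison remains valid.

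The sizes in steps 3 to 5 of the working rest on assumed severity shares of 30% or 50% and assumed odds ratios of 1 to 4. None of these comes from the article. That BPD severity predicts repeat self-harm is itself an assumption, though a reasonable one. If it is false, the covariate costs almost nothing (0.902 v 0.895 in the simulation).

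**What to change.** Before outcome data are examined by arm:
- Add the baseline number of SCID-II BPD criteria, not counting (e), as a prespecified covariate in the primary logistic model, next to sex and previous deliberate self-harm. If multiple imputation is used, include the count in the imputation model too.
- Confirm that all nine criteria are rated for each patient and that rating does not stop once two are met. The article does not say.
- State in the Discussion that eligible patients run from two traits to full BPD, so that conclusions are not limited to lesser severity.

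Eligibility, treatment and randomization stay as they are. The cost is one model term from data already collected and a sentence of text. A treatment-by-severity analysis is optional. If done, it should be labelled exploratory and reported as an interaction estimate with its confidence interval, which will be wide at this sample size.
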